## Abstract

**Background:**

Acute Coronary Syndromes account for 15% of deaths in the UK, and patients remain at significant risk of re-admission for future complications and death. Pathologically the underlying process of atherosclerosis is driven by inflammatory mechanisms, which are activated in ACS patients. Previous studies have investigated the role of inflammatory markers in this process, including interleukin 1 (IL-1) and C Reactive Protein (CRP). Pre-clinical studies indicate that IL-1 may be a primary driver of ACS and that the naturally occurring interleukin-1 receptor antagonist (IL-1ra) may inhibit the atherosclerotic process. This study will investigate the effects of IL-1ra on inflammatory markers in man.

**Methods/design:**

Three centres in the UK are planning to recruit 186 Non-ST elevation myocardial infarction patients to receive either interleukin-1 receptor antagonist (Anakinra) or matching placebo. Patients will receive a daily subcutaneous injection of either study drug or placebo over a 14 day period. The primary outcome is area under the curve of high sensitivity C-Reactive Protein (CRP) over the first 7 days.

**Discussion:**

The MRC-ILA-HEART Study is a proof of concept clinical trial investigating the effects of IL-1ra upon markers of inflammation in patients with Non-ST elevation myocardial infarction. It is hoped this will provide new and exciting information in relation to an "anti-inflammatory" strategy for patients with acute coronary syndrome.

**Trial registration:**

ISRCTN89369318

## Background

Acute coronary syndromes (ACS), caused by coronary atherosclerotic plaque destabilisation and interruption of coronary flow, are common, serious conditions that account for 15% of all deaths in the UK and are associated with considerable morbidity among survivors. ACS are classified by the presenting ECG: patients with persistent ST elevation myocardial infarction (STEMI) generally require early reperfusion [1], whereas those with non ST-elevation (NSTEMI) ACS require early risk stratification and revascularisation as necessary [2]. There remains, however, considerable risk in the non-ST elevation ACS patients: the average risk of death at 6 months is 6.2% with 19.3% re-attending hospital because of heart disease [3]. It is known that inflammatory processes are activated in ACS. This proposal is for a proof of concept clinical trial of a new and exciting anti-inflammatory strategy for the treatment of NSTEMI ACS based on pre-clinical investigations that we wish to translate to man.

### Inflammation and atherosclerosis

The past decade has seen a growth in treatment options available for ACS as a consequence of better understanding of the pathophysiology of this condition. At a biological level the process is driven by inflammatory mechanisms in the vessel wall where atherogenesis is initiated by lipids and other environmental agents [4,5]. Instability of the plaque atheroma so as to cause the disease to present is also viewed as an inflammatory process, predominantly where plaque macrophages destabilise the cap of the atheroma, resulting in the formation of an intra-coronary thrombus.

The therapeutic implications of these pathogenic pathways are that primary and, to some extent, secondary prevention are targeted at mutable risk factors (smoking cessation, blood pressure control, lipid lowering etc.) and anti-thrombotic strategies for the treatment and prevention of intracoronary thrombus. Evaluation of therapeutic strategies designed to treat the inflammatory processes involved in acute or chronic coronary artery disease (CAD) is at an early stage. Some agents may potentially have anti-inflammatory properties (statins in particular and fish oils) but this is not their primary mechanism of action and proving beneficial effects consequent upon the anti-inflammatory properties of these agents has been difficult.

Since the description of ACS as an inflammatory event potential sources of, and functions for, inflammatory cytokines in this process have been investigated [5,6]. IL-1 is an apical cytokine in the innate inflammatory response transducing signals from bacterial products through pattern recognition receptors, complement activation and TNFα. IL-1 has plausible actions in arterial wall inflammation in the setting of atherosclerosis, in particular its effects on endothelial cells (activation) and vascular smooth muscle cells (proliferation). There are two agonistic cytokines (IL-1α and IL-1β) that signal via the Type 1 IL-1 receptor and there is a specific Interleukin-1 receptor antagonist (IL-1ra), the only known naturally occurring cytokine antagonist, that inhibits IL-1 actions by binding to the Type 1 IL-1 Receptor (IL-1RI), blocking the receptor and preventing IL-1 from binding thereby preventing receptor signalling [7].

### Relevance of interleukin-1

The suggestion that IL-1 is involved in the pathogenesis of CAD, and in particular in ACS, is derived from a number of sources as there is no animal model of this condition. IL-1 and IL-1ra are expressed in diseased human coronary arteries [8,9]. Coronary artery IL-1β is up-regulated in porcine coronary arteries after balloon injury [10]. Genetic studies have indicated that polymorphic variants within the IL-1 cluster that have net pro-inflammatory effects are associated with angiographic CAD [11,12].

In mouse models of atherosclerosis IL-1ra inhibits the formation of intimal fatty streaks in apolipoprotein E-deficient mice [13], and IL-1β deficient mice when crossed onto an apo e-/- background have reduced atherosclerosis [14]. Relevant to vessel wall healing, we have data from mice and pigs that indicate the vessel wall response to injury (neointima formation) is an intensely IL-1 dependent event [15]. In the porcine coronary artery, the neointima response to balloon angioplasty (a model of arterial wall rupture in some way analogous to that which occurs in ACS) is reduced in its amount by a 14 day s.c. infusion of IL-1ra. We have crossed the IL-1R1-/- mouse with the apo e-/- and found reduced atherosclerosis. This double knockout, unable to signal IL-1, has no rise in blood pressure with fat feeding (in contrast to the apo e-/- control mice) and this is associated with reduced serum amyloid A levels (mice do not appear to have CRP), reduced markers of oxidative stress in the arterial wall and preservation of endothelial cell function in resistance arteries. We have reproduced the blood pressure rise inhibition and the modulation of oxidative stress seen in the IL-1R1-/-, apo e-/- double knockout by using s.c. IL-1ra treatment in apo e-/- mice.

In a cohort of 63 NSTEMI ACS patients we examined the impact of IL-1 gene polymorphisms upon markers of endothelial cell activation and CRP [16]. The intron 2, VNTR polymorphism that we have previously described as associated with reduced endothelial cell production of IL-1ra [17] (i.e. endothelial pro-inflammatory) was associated with significant increases in soluble markers of endothelial activation at the time of NSTEMI ACS, including the rise in plasma vWF, a marker known to be associated with clinical outcome [18].

Overall, our preliminary data indicate that 1) IL-1 is a potent mediator of arterial inflammation in the context of atherosclerosis and vessel wall injury and 2) IL-1 inhibition restores endothelial function, reduces inflammatory vessel wall responses and reduces vascular oxidative stress. We wish now to translate these findings to man.

### Markers of inflammation in ACS

ACS, as has been stated before, is an intensely inflammatory event at the level of the vessel wall. Data from angioscopy [19], angiography [20], IVUS [21] as well as functional cell biology [22] indicate that ACS is frequently associated with widespread coronary activation and inflammation, indicating a pancoronary inflammatory state. It has also become clear that serum markers of inflammation are predictors of complications following an episode of ACS and that statin therapy associated with lower achieved levels of CRP are associated with improvement in outcome [23]. These data suggest that modulation of inflammation in the coronary artery would be predicted to translate to clinical benefit. There is considerable interest in markers of outcome in ACS. These broadly fall into two groups; those that measure the size of the infarct and those that are measures of the pathogenic process in the vessel way and may reflect both the magnitude and duration of the process. In the former group are the markers of myocyte damage. Cardiac-specific Troponin is now recognised as a more sensitive and specific marker of myocardial necrosis than creatine kinase and its MB isoenzyme. Elevation of serum Troponin has been shown to identify patients with ACS at risk for adverse clinical outcomes [24-26].

In the latter group (markers of the pathological process) are the markers of inflammation, coagulation and of platelet activation. We believe that there are plausible links between IL-1 activation and these markers. The acute phase reactant C-reactive protein (CRP) is a strong predictor of cardiovascular events [27,28]. In NSTEMI ACS, treated with percutaneous coronary intervention (PCI), CRP rises and peaks between 24 and 48 hours [29]. It is clear, however, that in some patients there is persistent elevation with maybe 49% of patients having a CRP >3 mg/L at discharge and these patients were identified as having increased chances of recurrent admissions [30]. The absolute levels of CRP have been shown to have a high sensitivity (87%) and a low specificity (54%) for subsequent myocardial infarction in patients presenting with an ACS [31]. There is a difficulty using a percentage change in CRP, either for individual patients and predicting outcome or between two groups of (treated) patients, in that there is no baseline level from which comparisons can be made. Differences in outcomes in the PROVE-IT trial, however, were associated with differences in the achieved CRP level [23,32]. Biologically, CRP production by hepatocytes has to be induced and this has been shown to be driven by the IL-1 and IL-6 cytokines. Serum levels of IL-6 have been shown to be elevated in patients with ACS [33] and an elevation of IL-6 is an independent marker of increased mortality in ACS [30]. The relationship between IL-1 and IL-6 is well defined with IL-1 inducing IL-6 production [7]. It has, however, proved difficult to reliably measure IL-1β; a cytokine that is devoid of a signal sequence directing release and which probably circulates at a very low level.

During NSTEMI, a rise in von Willebrand Factor (vWF) between 24 and 48 h predicts adverse clinical events [18], and an association between circulating levels of IL-6 and von Willebrand factor (vWF) has recently been shown to determine prognosis in patients with ACS [34]. IL-1 has been shown to augment thrombin-induced release of vWF from human endothelial cells [35].

### Interleukin 1 receptor antagonist (IL-1ra)

There are two agonistic cytokines (IL-1α and IL-1β) that signal via the Type 1 IL-1 receptor (IL-1R1) and a specific Interleukin-1 receptor antagonist (IL-1ra), (the only known naturally occurring cytokine antagonist) that inhibits IL-1 actions by binding to the IL-1R1, blocking the receptor and preventing IL-1 from binding thereby preventing receptor signalling [7].

IL-1ra is available for the treatment of a number of inflammatory conditions as a recombinant, non-glycosylated, N-terminal methionine added protein (Kineret/Anakinra, Amgen). Although less successful than anti-TNF therapies in rheumatoid arthritis (RA), there appears to be considerable benefit in the management of Juvenile arthritis (Still's disease), and it is the treatment of choice in the rare autoinflammatory illnesses typified by Muckle-Wells syndrome. From all of the indications in which IL-1ra has been used it has emerged that IL-1ra is a very safe form of treatment and appears to be devoid of the side-effect of re-activation of infectious illness seen with anti-TNF therapies. The only problems encountered are mild, reversible injection site reactions and neutropaenia in <1% of patients after a month or more of treatment.

Dosing with IL-1ra is simple. A single, daily, subcutaneous 100 mg injection of IL-1ra is the standard dose of IL-1ra for all individuals with normal renal function. In RA this causes a 35% reduction in CRP after approximately 1 week of treatment. Higher doses do not achieve any greater reduction in CRP of relief of RA symptoms. Single daily dosing schedules are used in the sucessful treatment of Juvenile arthritis and Muckle-Wells. The half-life of IL-1ra is 4–6 hours with maximum absorption from an s.c. injection at 3–7 hours. (Data on file supplied by Amgen).

## Conclusion

All of these data indicate that the IL-1 cytokine has the potential to act as a primary driver of ACS. Prolonged coronary activation is associated with worse outcome in ACS. It is therefore plausible that blockade of the IL-1 system could be of therapeutic benefit. We believe our pre-clinical data indicates that a purely anti-inflammatory approach based upon Interleukin-1 (IL-1) inhibition using IL-1 receptor antagonist (IL-1ra) is a feasible and logical therapy for ACS and this approach could open a new therapeutic paradigm for evaluation in further studies.

### Aim of study

The main objective is to assess whether treatment of NSTEMI ACS with IL-1ra alters the inflammatory process involved in this condition

### Trial design

Randomised, double blind, placebo-controlled multi-centre phase II clinical trial

### Eligibility

#### Inclusion criteria

1. Acute cardiac chest pain consistent with an acute coronary syndrome

2. <48 hours from onset of symptoms that led to hospital admission

3. And at least one of the following:

a) A raised troponin as defined by local parameters specified at each centre

b) Other ECG changes consistent with acute myocardial ischaemia (e.g. Horizontal or down-sloping ST depression of at least 0.5 mm or T-wave inversion of at least 3 mm, in at least two leads of the ECG, or new onset bundle branch block) and an elevated level of Troponin above local laboratory values indicating myocardial damage

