### Study treatment

Eligible patients will be randomised in equal proportions between IL-1ra and placebo, receiving either a once daily, subcutaneous (s.c). injection of IL-1ra (dose 100 mg per 24 h) for 14 days, or a daily s.c. injection of placebo for 14 days. The hospital pharmacist will issue the relevant drug package. (Please see appendices for pharmacy information).

The study drug and placebo will be provided by Amgen Inc in its commercially available recombinant form which is in clinical use for the treatment of arthritic conditions. The study drug and placebo will be relabelled by Amgen, in collaboration with CTEU according to MHRA guidelines.

The first dose of IL-1ra will be given within 24 h +2 h of the positive Troponin. Injections will be given at a standardised time (24 ± 2 h after the previous dose), immediately after blood sampling. IL-1ra or placebo will administered to the patient by the research nurse while the patient is in hospital. During the hospital stay, the patient will be taught to self-administer the injection by the research nurse and on discharge will continue at home. This has proven possible in other ACS trials that required self injection of subcutaneous heparin [36]. Full written guidance on self injection will also be provided to patients. If self injection is found not to be possible in an individual patient for unexpected reasons, an alternative method will be sought (e.g. district nurse, or attending the hospital) to try and maintain full compliance with scheduled study drug regimen after discharge. Patients will also be asked to complete a daily injection diary. All personnel will be blinded to the identity of the syringe contents.

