### Study related investigations and follow-up

Patients will have blood taken every day for seven days for hsCRP (baseline and days 1–7, 14 and 30), Troponin (baseline and days 1–7 and 14), full blood count (baseline, days 7 and 14), creatinine, electrolytes, liver function tests (baseline, days 1–7 and 14), Interleukin-6 and von Willebrand factor (baseline, days 1–3,14,30). Blood will be taken prior to administration of either IL-1ra or placebo. A summary of samples and study related procedures to be undertaken is shown in Table 1. If the patient is discharged before the seventh day, they will be required to attend clinic to have the remaining blood samples taken.

**Table 1 T1:** Study procedures

Procedure	Baseline	Days 1 – 7	Days 8–13	Day 14	Day 30 (end of study)
Clinical evaluation	√	√		√	√
Informed consent	√				
Randomisation	√				
ECG	√	√		√	
Study drug given		√	√	√	
Full blood count	√	√		√	
Creatinine, electrolytes, eGFR	√	√		√	
Troponin	√	√		√	
hsCRP	√	√		√	√
Liver function tests	√			√	
IL-6, vWF	√	√		√	√
Post discharge follow up visit				√	√
Samples for DNA & RNA	√				√
Cardiac magnetic resonance scan (1)		√			√
ST segment monitoring (2)		√			
Forearm endothelial study (3)		√		√	

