### Outcome measures

#### Primary outcome measure (comparison of treatment group with control)

Area under the curve of serum high sensitivity CRP over the first 7 days

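### Patients can enter the 7-day CRP AUC and the vWF/IL-6 series at different phases of the acute response, and the primary ANOVA names no term for time since symptom onset

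*Protocol article*

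**What the plan says.** - **Entry clock (Inclusion criteria, item 2):** "<48 hours from onset of symptoms that led to hospital admission".
- **Dosing clock (Study treatment):** "The first dose of IL-1ra will be given within 24 h +2 h of the positive Troponin". This runs from the troponin result. No limit from symptom onset to first dose is given.
- **Outcome clock (Primary outcome measure):** "Area under the curve of serum high sensitivity CRP over the first 7 days". The days are study days.
- **Sampling (Study related investigations and follow-up):** "hsCRP (baseline and days 1–7, 14 and 30") for CRP, and "Interleukin-6 and von Willebrand factor (baseline, days 1–3,14,30") for the other two markers. "Blood will be taken prior to administration of either IL-1ra or placebo". Table 1 shows study drug from Day 1 and none at baseline.
- **Cited kinetics (Markers of inflammation in ACS):** for NSTEMI treated with PCI, "CRP rises and peaks between 24 and 48 hours"; and, during NSTEMI, "a rise in von Willebrand Factor (vWF) between 24 and 48 h predicts adverse clinical events". Neither sentence says what the hours are counted from.
- **Analysis (Randomisation; Primary analysis):** stratification is by centre and by glycoprotein IIb/IIIa use. The log AUC is analysed by ANOVA, and neither time since onset nor baseline CRP is named.

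**The concern.** The markers rise and fall over a few days, so the value on a given study day depends partly on how far into the event the patient was at entry. An early entrant contributes the rise, peak and decline to the 7-day AUC. A late entrant may contribute mainly the decline. The protocol's own background describes kinetics on a scale of one to two days, the same scale as the spread in entry and dosing times that it permits.

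Two things are at stake. First, variation in log AUC that could be explained stays in the error term. Second, if the trial finds no effect on CRP, vWF or IL-6, an analysis without onset time gives little help in telling an inactive treatment from one started late in the response.

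Baseline CRP alone does not settle the matter. A low baseline value can mean that CRP has not yet risen (early entry) or that the response is small (late entry). The background section itself remarks that there is no baseline level from which change can be judged. Onset time supplies part of that missing reference.

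**Working it through.** **1. The plan's own sample size.** Inputs from Sample size: standardised difference 0.45, 80% power, 5% significance (taken as two-sided), about 80 per group.
- n = 2 × ((1.960 + 0.842)/0.45)² = 77.5, so 78 per group. This agrees with about 80.
- Power at 80 per group: standard error = √(2/80) = 0.158; 0.45/0.158 = 2.846; Φ(2.846 − 1.960) = 81.2%.

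**2. Latest first dose the text permits.** A troponin that turns positive just under 48 h after onset allows a first dose at up to 48 + 24 = 72 h, or 48 + 26 = 74 h with the tolerance.

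**3. First sample that can show an effect.** Drug starts on Day 1 and blood is drawn before each dose, so the Day 1 sample is pre-treatment. Day 2, 24 ± 2 h after the first dose, is the first post-dose sample. For vWF and IL-6 the early post-dose samples are Days 2 and 3 only.

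**4. SD of log AUC implied by the plan.** If the one-third reduction is the ratio 2/3, then |ln(2/3)|/0.45 = 0.405/0.45 = 0.90, and the variance is 0.81.

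**5. Effect of entry time on AUC (assumed curves; the documents give none).** CRP has a base of 3 mg/L, a linear rise of 30 mg/L to a peak at 24, 36 or 48 h from onset, then exponential decay of the excess with a half-life of 24, 48 or 72 h. AUC is taken over 168 h from entry, with identical disease and no treatment.
- Ratio of AUC, entry at 48 h against entry at 6 h: from 1019/1867 = 0.55 (peak 24 h, half-life 24 h) to 3002/3403 = 0.88 (peak 48 h, half-life 72 h).
- This compares the two extremes of entry. What matters for power is the share of variance.

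**6. Share of variance from onset time alone.** With entry uniform over 6–48 h (assumption), the SD of log AUC due to timing is 0.039–0.193 across the nine curves.
- Share: 0.039²/0.81 = 0.2% to 0.193²/0.81 = 4.6%.
- Power after perfect adjustment at the upper end: 0.45/√(1 − 0.046) = 0.461; 0.461/0.158 = 2.914; Φ(0.954) = 83.0%. At the lower end it stays at about 81%.
- Harsher case, half of patients at 6 h and half at 48 h: share 0.5–11%, power at most about 86%.

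**7. Onset time beside baseline CRP.** In an illustrative simulation, the time term raised R² for log AUC by a further 0.07–0.27 beyond log baseline hsCRP. The range depends on the assumed curves, spread of peak height and sampling noise. It shows why the two terms belong together but does not estimate the gain in this trial.

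**8. Interpretability (illustration).** If 20% of patients started late and kept half the effect, the average standardised difference would be 0.45 × (0.8 + 0.2 × 0.5) = 0.405 and power 73%. If they kept none, it would be 0.36 and 62%. The documents give neither the share nor the effect retained, and a covariate would not recover this loss.

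**The case against.** The strongest case against is that this is a small refinement of a kind usually left to the analysis plan, which is not shown. Several stronger readings are tempting, and the documents do not support them.

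- **That treatment may start after the CRP peak.** A reader might count the 24–48 h from symptom onset. The protocol gives no time origin and ties the CRP sentence to PCI. If the clock starts at PCI, the peak may follow the first dose.
- **That entry time moves the AUC by as much as the effect sought.** A reader might set the 12–45% gap between the extreme entry times beside the one-third reduction. The gap is between individual patients at the limits of entry; the reduction is a difference between arm averages. As a share of variance, timing is small.
- **That the trial misses its vWF endpoint.** If the clock were onset, only patients first dosed by about 24 h would have a post-dose vWF sample by 48 h. But no endpoint is a rise at 24–48 h. The outcome is vWF and IL-6 at the scheduled times.
- **That the arms are biased.** Randomisation balances onset time in expectation.

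Two further points count against a heavier grade. Screening and recruitment are to be as soon as possible, so very late dosing may be uncommon. Fourteen days of dosing, with CRP also compared at days 7, 14 and 30, can still show an effect on persistent inflammation.

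These arguments limit the size of the point but do not remove it. The protocol itself fixes the entry and dosing clocks, the study-day outcome and an ANOVA, so the missing term is a feature of the stated analysis.

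**Conclusion.** The point holds as a modest improvement in precision and interpretation. The permitted spread in entry and dosing times means that patients start the CRP, vWF and IL-6 series at different phases, and the stated ANOVA does not account for this. Onset time alone explains about 0.2–5% of log-AUC variance, worth at most about 2 percentage points of power with entry spread evenly over 6–48 h. These figures rest on the assumed CRP curves, that spread of entry, and the SD of 0.90 inferred from the sample-size statement. Used with baseline hsCRP, onset time may do more, but by how much cannot be read from the documents. The number of late starters is also unknown, so the power losses in step 8 are illustrations. The finding does not show bias, a missed peak or a failed vWF endpoint.

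**What to change.** - **Primary model:** replace the plain ANOVA of log AUC with an ANCOVA that pre-specifies hours from symptom onset to randomisation and log baseline hsCRP. Time to randomisation is preferable to time to first dose because it is fixed before allocation.
- **vWF and IL-6:** compare the arms on post-dose samples, Day 2 onward, adjusting for the same time term and the marker's own baseline. Treat Day 1 as a pre-treatment sample.
- **Data:** make sure that the time of symptom onset is recorded for analysis. Inclusion criterion 2 cannot be checked without it.
- **Consistency:** the investigators should reconcile the entry window, the first-dose window and the cited kinetics, and state what the 24–48 h is counted from. No clinical window is proposed here.

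The cost is wording and two covariates in each model. No visit, sample or dose changes. A split at 24 h from onset would add little, since it divides about 160 evaluable patients into imprecise subgroups.
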